## Abstract

**Background:**

Many prediction models have been developed to help identify emergency department (ED) patients at high risk of poor outcome. However, these models often underperform in clinical practice and their actual clinical impact has hardly ever been evaluated. We aim to perform a clinical trial to investigate the clinical impact of a prediction model based on machine learning (ML) technology.

**Methods:**

The study is a prospective, randomized, open-label, non-inferiority pilot clinical trial. We will investigate the clinical impact of a prediction model based on ML technology, the RISK^INDEX^, which has been developed to predict the risk of 31-day mortality based on the results of laboratory tests and demographic characteristics. In previous studies, the RISK^INDEX^ was shown to outperform internal medicine specialists and to have high discriminatory performance. Adults patients (18 years or older) will be recruited in the ED. All participants will be randomly assigned to the control group or the intervention group in a 1:1 ratio. Participants in the control group will receive care as usual in which the study team asks the attending physicians questions about their clinical intuition. Participants in the intervention group will also receive care as usual, but in addition to asking the clinical impression questions, the study team presents the RISK^INDEX^ to the attending physician in order to assess the extent to which clinical treatment is influenced by the results.

**Discussion:**

This pilot clinical trial investigates the clinical impact and implementation of an ML based prediction model in the ED. By assessing the clinical impact and prognostic accuracy of the RISK^INDEX^, this study aims to contribute valuable insights to optimize patient care and inform future research in the field of ML based clinical prediction models.

**Trial registration:**

ClinicalTrials.gov NCT05497830. Machine Learning for Risk Stratification in the Emergency Department (MARS-ED). Registered on August 11, 2022. URL: https://clinicaltrials.gov/study/NCT05497830.

**Supplementary Information:**

The online version contains supplementary material available at 10.1186/s13049-024-01177-2.

## Introduction

The accurate assessment of the severity of the patient’s disease is an important challenge for physicians in the emergency department (ED). As the number of patients who visit the ED increases worldwide, crowding increases pressure on ED physicians, affecting not only patient satisfaction, but also placing the patient at risk of delayed treatment, increased in-hospital length of stay and increased mortality [1–5]. Fast and reliable discrimination between high and low risk patients may assist in proper allocation and management of resources, improving acute healthcare for patients in the ED.

Stratification of ED patients into low and high risk of poor outcome has traditionally relied on the clinical intuition of ED physicians and nurses [6]. However, previous studies have shown that ED physicians experience a high cognitive load, having to make important clinical decisions for their patients, often based on incomplete data, while being interrupted regularly and attending several patients at the same time [7–9]. Several clinical prediction models, e.g. modified early warning score (MEWS), sepsis-related organ failure (SOFA) score, and risk stratification in the ED in acutely ill older patients (RISE UP), have been developed to aid clinical decision-making [10–12]. Since many models have not been externally validated, their discriminatory performance may be overestimated. Furthermore, implementation of these models may be difficult because some of them have been developed for a specific diagnosis, which may not yet have been established in the ED. Given the heterogeneity of ED patients, finding a single prediction model that covers the entire clinical spectrum remains difficult [13].

Recently, machine learning (ML) technology has emerged as a promising approach to develop new prediction models [14, 15]. One such new prediction model, the RISK^INDEX^, has been developed at the Maastricht University Medical Center (MUMC+) [16]. The RISK^INDEX^ utilizes sex, age and routine laboratory tests from the ED to predict 31-day mortality. The RISK^INDEX^ was externally validated in three other medical centers demonstrating an AUC of 0.88 to 0.98 ^16^. Although ML based prediction models show great potential, to our knowledge, randomized clinical trials to investigate their actual clinical impact have rarely been performed.

In this context, the MARS-ED study aims to evaluate the clinical impact of the RISK^INDEX^ in the ED. This pilot randomized study will assess both the magnitude of the clinical impact and the prognostic accuracy of the RISK^INDEX^ in a large study sample.

## Methods

### Study objectives and endpoints

The primary objective of this study is to assess the prognostic accuracy and the clinical impact of the RISK^INDEX^ prediction model. Secondary objectives of this study are to assess: (1) the number and type of changes in medical treatment after presentation of the RISK^INDEX^ to the ED physician; and (2) the prognostic accuracy of the RISK^INDEX^ as compared to that of the physician’s clinical intuition and that of other clinical prediction models (e.g. MEWS, SOFA, RISE UP score).

### Trial design and setting

The MARS-ED study is designed as an investigator-initiated, open-label, randomized, non-inferiority, pilot clinical trial. Adult patients presenting to the ED who are primarily assessed and treated by an internal medicine specialist will be randomized in a 1:1 ratio to the control group or the intervention group. This study is not blinded, since the physician needs to be informed of the RISK^INDEX^ in order to assess the size of the clinical impact of the RISK^INDEX^.

The study will be conducted in the ED of the MUMC+, which is a secondary/tertiary care medical center in the Netherlands, with 5,500 patients visiting the ED for assessment by an internal medicine specialist each year. In contrast to many other countries where patients can visit the ED without referral by a health care professional (open access ED), nearly all ED patients in the Netherlands after referred after an initial triage process by a general practitioner, a medical specialist or ambulance.

This study protocol is designed in accordance with the Standard Protocol Items: Recommendations for Interventional Trials - Artificial Intelligence (SPIRIT-AI) and the Consorted Standards of Reporting Trials (CONSORT) guidelines (Supplementary Table 1) [17, 18]. This study has been approved by the medical ethical committee (METC) of the MUMC + on June 21st 2022 (METC 21–068) and is registered at clinicaltrials.gov (NCT05497830). The study will be conducted according to the principles of the Declaration of Helsinki (version 2013, July 9th 2018) and in accordance with the standards of Good Clinical Practice. The study is expected to last from September 2022 to September 2024.

### Recruitment and selection of eligible patients

All adult ED patients (18 years or older) who are assessed and treated by internal medicine specialist or their residents and who meet the inclusion criteria will be asked informed consent to participate in this study by a member of the research team.

As patients may be unconscious, in a state of delirium or otherwise unable to provide informed consent, a legal representative may make the decision on participation as well. In case of absence of such representative, a deferred consent procedure may take place, in which consent is implied and randomization will take place according to the study protocol and the patient will receive medical care as usual [19]. Within 72 h after randomization, a member of the research team will contact the patient to ask for informed consent. If this is not possible, e.g. because the patient has already been discharged from the hospital before a member of the research team was able to contact the patient, the patient dies before giving informed consent, or the patient (or representative) remains unable (or unavailable) to give informed consent for more than 72 h after randomization, data of this patient will be deleted.

### Study intervention and procedure

When a patient enters the ED for assessment and treatment by an internal medicine specialist, the patient will immediately be assessed for eligibility and randomized as soon as informed consent is obtained. Obtaining informed consent is performed by a member of the research team and involves explaining the study intervention and procedure to the patient and handing out a patient information form. The inclusion criteria and exclusion criteria are shown in Table 1.

**Table 1 Tab1:** Inclusion and exclusion criteria

Inclusion criteria	Exclusion criteria
Patients must meet all of the following criteria: - Adult (18 years or older) - Primarily assessed and treated by an internal medicine specialist in the ED - At least 4 laboratory test results available within the first 2 h of the ED visit - Willing to provide written informed consent (either directly or after deferred consent)	Patients who meet any of the following criteria: - Less than 4 laboratory test results available within the first 2 h of the ED visit - Unwilling to provide written informed consent

ED, emergency department

After inclusion, the patient is allocated to either the intervention group or the control group through randomization. An overview of the patient’s timeline is shown in Supplemental Fig. 1. Then, the patients will receive medical care in the ED as usual. After complete assessment of the patient, in both the intervention group and control group, the physicians will be asked questions regarding their clinical intuition (Table 2). In the intervention group, the RISK^INDEX^ will be presented to the physician together with the average mortality risk for ED patients with the same age and sex, and subsequently questions will be asked concerning agreement of their clinical intuition with the RISK^INDEX^ and whether the presented RISK^INDEX^ leads to changes in the treatment plan (Table 2). If the patient is admitted to the hospital, the attending physician on the medical ward will be asked the questions regarding clinical intuition on the first day of admission. A member of the research team immediately records the answers to the questions of all questionnaires in an electronic case record form, which was specially designed for this study.

**Table 2 Tab2:** Questionnaires regarding clinical intuition and medical treatment changes

**Questionnaire regarding clinical intuition (both intervention group and control group)**
- Surprise question: “Would you be surprised if this patient dies within the next 31 days?” (yes/no) [20, 21] - Concern question: “How concerned are you about the health of this patient?” (Likert scale 1–10) [6] - Severity question: “How severely ill do you find this patient?” (Likert scale 1–10) [22] - “Do you think that this patient will be admitted to the hospital for more than 7 days?” (yes/no) - “Do you think that this patient will be admitted to the ICU?” (yes/no)
**Questionnaire regarding medical treatment changes (intervention group only)**
- “Is the RISK^INDEX^ higher than, equal to, or lower than you expected?” - “Do you want to alter the medical treatment plan based on the RISK^INDEX^?” (yes/no) - “If yes, which part of the treatment plan?“ (reassessment during current ED visit; order additional investigations and consultations; admission or discharge; consultation with an ICU specialist and/or admission to ICU; removing or emplacing treatment restrictions) ^a^

ED, emergency department; ICU, intensive care unit

^a^ The physician will be asked to specify which part of the treatment plan was altered by choosing any of the given options

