### Sample size

This pilot trial has an explorative aim, providing future trials with estimates of effect sizes and potential clinical impact of the RISK^INDEX^. This study aims to provide robust estimates for the likely recruitment and retention rates and give an indication of the potential variability in the proposed outcome measures, which will in turn be used to inform the power calculation for a future definitive randomized controlled trial (RCT). We calculated a required sample size of 784 patients to detect a 2% difference in the number of changes in medical treatment after presentation of the RISK^INDEX^ between the control group and the intervention group with a power of 0.8.

Yearly, approximately 5,500 patients are treated by an internal medicine specialist at the ED of MUMC+. Considering fluctuations in the number of patients presenting to the ED and moments of crowding, there may be moments where there will not be enough time to include patients and/or to complete the questionnaires. Therefore, we expect a total sample size of 1300 patients during the inclusion period.

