### Statistical analysis

All analyses will be performed using the SPSS software (IBM Corp. Released 2021. IBM SPSS Statistics for Windows, version 28.0. Armonk, NY: IBM Corp).

The prognostic accuracy of the RISK^INDEX^ and the physician’s clinical intuition to predict adverse outcomes will be analyzed using an area under the receiver operating characteristics curve (AUC). To assess the clinical impact of the RISK^INDEX^, the number of changes in medical treatment based on the RISK^INDEX^ will be calculated. The prognostic accuracy of the RISK^INDEX^ will also be compared to that of the physician’s clinical intuition and to that of other clinical prediction models. Sub-analyses will be performed on the ED physicians’ characteristics, i.e. level of experience and function in relation to the accuracy of their clinical intuition. Summary estimates of effects will be presented along with their 95% confidence intervals (CI). Differences between the intervention and control groups will be presented in the form of an unadjusted mean difference for continuous outcomes, and an odds ratio for binary outcomes. Exploratory analysis using ANCOVA for continuous variables and logistic regression for binary outcomes will consider adjustment for the stratification variables in assessment of the treatment effects. Baseline characteristics will be summarized for all patients, and separately for the intervention group and control group. Feasibility and process evaluation data, such as practice recruitment rate, implementation and uptake of and adherence to the intervention, and follow-up rates will be summarized and presented as percentages.

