## Discussion

Rapid and accurate risk stratification at the ED is essential to optimize patient care and improving outcomes. Various prediction models, ranging from models based on a set of laboratory tests and vital signs (e.g. MEWS, SOFA, RISE UP) to emerging models based on ML have been proposed to aid in this stratification. Unfortunately, most of these models lack external validation, precision, or generalizability to the heterogeneous ED population [13]. In line with the emerging trend of ML technology based prediction models, we developed the RISK^INDEX^, a ML based prediction model that uses demographic characteristics (i.e. age and sex) and the results of laboratory tests available within the first two hours of ED presentation to create an individualized, precise and rapid risk estimation of 31-day mortality. The RISK^INDEX^ has externally been validated in three other hospitals, showing high prognostic accuracy (AUC ranging from 0.88 to 0.98) [16]. To the best of our knowledge, the MARS-ED study is the first prospective, randomized study to investigate the clinical impact of a ML based prediction model in the ED.

We aim to investigate the clinical impact of the RISK^INDEX^ by reviewing the number of changes in the medical treatment plan made as a result of presentation of the RISK^INDEX^ to the ED physician. In addition, we aim to prospectively investigate both the prognostic accuracy of the RISK^INDEX^ and the clinical impact of such a predictive model, and compare the RISK^INDEX^ to the physician’s clinical intuition. By randomizing the patients into an intervention group and a control group, we also aim to assess the clinical impact by comparing the treatment plan in both groups. The ultimate goal of this pilot study is to provide future studies with meaningful estimates of clinical impact of a ML based clinical prediction model.

While a limited number of retrospective studies have described attempts to use ML technology for risk stratification in the ED, none of these studies have been prospectively validated in a randomized setting [14, 15, 26, 27]. In other studies, ML based prediction models were developed with prognostic accuracies similar to our study (AUC of 0.96 and 0.93) [26, 27]. However, to our knowledge, no prospective, randomized trials validating these models have been conducted.

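### The trial is sized on a between-arm difference in treatment changes, but changes are recorded only in the intervention arm, so the control term is zero by definition and not measured

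*Protocol article*

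**What the plan says.** The Sample size section of the protocol article gives a total of 784 at power 0.8 and words its target as follows: "detect a 2% difference in the number of changes in medical treatment after presentation of the RISK^INDEX^ between the control group". The other side of that contrast is the intervention arm. The section expects 1300 patients in total.

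Study intervention and procedure describes what happens at the bedside. Physicians in both arms answer the clinical-intuition questions. In the intervention arm only, the RISK INDEX is then displayed and the physician is asked whether it changes the plan. Table 2 heads that second set of questions "Questionnaire regarding medical treatment changes (intervention group only". Its yes/no item asks about altering the plan because of the index, followed by five categories of change. The later ward contact on the first day of admission repeats the intuition questions and has no change item.

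On analysis, the Statistical analysis section says that, for clinical impact, "the number of changes in medical treatment based on the RISK^INDEX^ will be calculated". It also plans odds ratios between arms for binary outcomes. The Discussion adds: "we also aim to assess the clinical impact by comparing the treatment plan in both groups".

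**The concern.** A difference between two arms needs the same quantity observed in both. Here the endpoint that sets the sample size is observed in one arm, through a question that has no meaning in the other. An analysis plan cannot repair this, because it concerns what is recorded at the bedside.

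Intervention physicians have just answered five reflective questions, see a mortality score, and are then asked by a study team member whether they want to change the plan. Some changes could follow from the reflection or from being asked. A control arm asked a matching question would show how many; the design as described does not. Clinical impact is part of the primary objective, and the pilot exists to hand effect estimates to a later trial. That trial would inherit a comparator that was set to zero and never observed.

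**Working it through.** **1. What is recorded, by arm.** The five change categories of Table 2, set against the outcomes listed in Data collection methods (not restricted to one arm):

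| Change type in Table 2 | Recorded as a change, intervention | Recorded as a change, control | Related end state collected in both arms |
|---|---|---|---|
| Reassessment in the ED | yes | no | none listed |
| Extra investigations or consultations | yes | no | none listed |
| Admission or discharge | yes | no | hospital admission |
| ICU consultation or admission | yes | no | ICU admission |
| Treatment restrictions | yes | no | treatment restrictions |

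Three of five types have a between-arm counterpart. Each counterpart is an end state, not a change of plan.

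**2. Inputs for the sample size.**
- Target: "We calculated a required sample size of 784 patients to detect a 2% difference in the number of changes in medical treatment", read as 2 percentage points in the proportion of patients with a change.
- Contrast and power: "between the control group and the intervention group with a power of 0.8".
- Allocation: patients "will be randomized in a 1:1 ratio to the control group or the intervention group", so 784 / 2 = 392 per arm and 1300 / 2 = 650 per arm.
- Alpha: not stated for this calculation. Two-sided 0.05 is assumed, in line with estimates "presented along with their 95% confidence intervals (CI".
- Control rate: not stated.

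**3. Reproducing 784.** For two proportions with pooled variance, where q = 1 − p, p̄ is the mean of the two rates and δ their difference:

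n per arm = [1.960·√(2p̄q̄) + 0.842·√(p₀q₀ + p₁q₁)]² / δ²

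With p₀ = 0 and p₁ = 0.02, so p̄ = 0.01: [1.960·√0.0198 + 0.842·√0.0196]² / 0.0004 = (0.2758 + 0.1178)² / 0.0004 ≈ 387.3. That rounds up to 388 per arm, 776 in total, 1.0% below 784. Power at 392 per arm is 80.5%.

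None of the non-zero control rates tried (0.5% to 49%) gives a total near 784, one- or two-sided, with or without continuity correction. The match to 0% versus 2% is not unique, however. A standardised difference of 0.2 gives 4·[(1.960 + 0.842)/0.2]² ≈ 784.9, and 0% versus 2% at one-sided 0.05 with continuity correction gives 798.

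**4. If the control rate were measured and not zero.** Power = Φ{[δ√n − 1.960·√(2p̄q̄)] / √(p₀q₀ + p₁q₁)}. For 1% versus 3% at n = 392: (0.02·19.799 − 0.3881) / 0.1975 = 0.040, so power is 52%. For a 2-point difference, two-sided 0.05:

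| Assumed control rate | Total N for 80% power | Power at 784 | Power at 1300 |
|---|---|---|---|
| 0% | 776 | 80% | 95% |
| 0.5% | 1158 | 63% | 84% |
| 1% | 1538 | 52% | 73% |
| 2% | 2282 | 37% | 56% |
| 5% | 4426 | 22% | 33% |
| 10% | 7682 | 14% | 21% |

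**5. If the endpoint is read as a one-arm proportion.** The 95% CI half-width with 392 patients at a true rate of 2% is 1.96·√(0.02·0.98/392) = 0.0139, about 1.4 points. At 5% it is about 2.2 points and at 10% about 3.0.

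**The case against.** The strongest reply is that the item asks the physician to attribute the change to the index. Where no index is shown, such changes are zero by definition, and 784 is compatible with 0% versus 2%. A reader might infer from the missing control item that the difference cannot be estimated at all. That goes too far: a number exists, but it is the intervention-arm proportion presented as a contrast. Equally, the near match does not prove that the authors used a zero control rate, since other inputs come as close.

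A reader might also infer that the trial makes no use of randomisation for clinical impact. The document does not support that. Admission, ICU admission and treatment restrictions are collected without restriction to one arm, and between-arm odds ratios are planned. These are simply not the endpoint that sets the sample size.

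A third tempting inference is that a large share of the targeted 2% would be prompting and not the index. Nothing in the document gives a size for that effect, and a physician moved only by reflection should answer no to an attributional question. Misattribution is possible; its extent is unknown.

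Finally, this is an exploratory pilot, the number and type of changes is listed as a secondary objective, and the article is condensed, with a supplementary figure not shown. This tempers the weight of the point. It does not remove it: the article says positively which arm gets which questions, and the Statistical analysis section uses the same count to represent clinical impact.

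**Conclusion.** The point holds as an inconsistency between the stated sample-size contrast and the stated measurement. The between-arm difference that justifies 784 patients has a control term fixed at zero by the wording of the question. The resulting impact figure is a one-arm proportion, to which randomisation adds nothing, and changes caused by the index are not separable in it from changes caused by reflection or by being asked.

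The consequence for power depends on a control rate that the document does not give. If changes were measured the same way in both arms and the control rate were 1%, power for a 2-point difference would be 52% at 784 patients and 73% at 1300; at 2% it would be 37% and 56%. These figures assume two-sided 0.05 and a difference in percentage points.

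**What to change.** Choose one of two repairs.

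**(a) Make it a real contrast.** Ask a parallel alter-the-plan question with the same five categories in both arms, directly after the intuition questions: without the index in controls, and after its display in the intervention arm. Compare arms with a risk difference and 95% CI. Keep the question that attributes the change to the index as a descriptive intervention-arm item. Restate the power with an explicit control rate, since any measured background rate breaks the present claim (table in the working). Cost: a few eCRF fields, an amendment and slight prompting of control physicians. Control-arm answers for patients already enrolled cannot be recovered.

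**(b) Call it what it is.** Restate the Sample size target as an intervention-arm proportion justified by precision (half-width about 1.4 points at 2% with 392 patients). Drop the between-arm power claim for this endpoint, and name admission, ICU admission and treatment restrictions as the between-arm impact outcomes. Cost: text only, and a less favourable stated claim. The effects of reflection and of being asked remain inseparable from the index in the reported proportion.
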